#### Randomization

The design will follow CONSORT randomization guidelines [31]. Participants will be eligible for randomization once all baseline questionnaires are completed. Blocked randomization will be conducted using a randomization table. Subjects in each block will be assigned to one of three intervention arms, ensuring equal allocation between CN and MCI subjects in each group.

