Individuals meeting these pre-screening criteria will then be scheduled for an in-person screening visit to provide written informed consent and further assess eligibility criteria via a 7-day screening period. After signatures are obtained, each prospective subject will be provided with a copy of the signed informed consent document. All procedures have been approved by the University of Miami Institutional Review Board (IRB) requirements and federal privacy protections and will be conducted in accordance with the Helsinki Declaration. Thereafter, prospective participants will be randomized into one of three arms and will receive intervention-specific, wearable devices and will be instructed on how to use these devices. All prospective participants will receive Fitbit devices, while those assigned to sleep or sleep + exercise intervention will receive an Elemind Neuromodulation headband to be used daily without stimulation during the initial 7-day screening period and a Lys device. Prospective participants in all groups will be asked to wear the Fitbit device continuously to establish baseline physical activity levels and to confirm sedentary to lightly active physical activity levels in order to satisfy eligibility criteria for those assigned to interventions that involve exercise, and those assigned to the sleep-only or sleep + exercise interventions will be asked to wear the Elemind Neuromodulation headband without stimulation while the device actively collects sleep data for seven consecutive nights to establish baseline sleep patterns, ensure comprehension of and comfortability with wearing the headband; additionally, this will confirm subquality sleep pre-intervention to satisfy eligibility criteria for those assigned to groups that involve the sleep intervention.

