Prospective participants who are assigned to the sleep or sleep + exercise interventions and are determined to have good quality sleep after the onboarding period as defined by the eligibility criteria will either be reassigned to the exercise-only intervention (if also found to engage in < 150 minutes of moderate-level or < 75 minutes of vigorous-level activity weekly via the Fitbit) or will be excluded from further participation and given $20 compensation. Prospective participants who are assigned to the exercise or sleep + exercise interventions and who are found to be active or very active (as defined by the eligibility criteria) will either be reassigned to the sleep-only intervention and be invited to undergo an additional 7-day onboarding screening duration with the Elemind Neuromodulation headband to determine sleep-specific eligibility or will be excluded from further participation and given $20 compensation. Prospective subjects who agree to undergo an additional 7-day screening period and are deemed to have good quality sleep pre-intervention at baseline will also be excluded from participation and given $20 compensation.

Once a participant has completed the 7-day onboarding screening period and found to be eligible, subjects will be prompted to set up an appointment with Quest Diagnostics. Sample analysis will be available to the participant through email and/or through the Quest Diagnostics app within a few days, and participants will consent to share the data with the University of Miami study team. Intervention (week 0) will begin as soon as possible after this process is complete. Another identical procedure will be initiated as soon as possible after the intervention period is complete. All procedures will comply with the University of Miami Institutional Review Board (IRB) requirements and federal privacy protections. Subsequent to completing the onboarding screening period, eligible participants will be invited to complete an in-person baseline visit.

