#### Baseline and follow-up visits

Data will be collected at baseline, biweekly, and at the 8-week follow-up to assess changes in sleep, exercise, biomarkers, and cognition. After consent and randomization, participants will be onboarded in person to each intervention-specific device and observed for a 7-day period prior to the baseline visit to establish baseline sleep patterns and/or physical activity levels relevant for each assigned intervention and to ensure all eligibility criteria are satisfied. Cognitive function will be measured using an augmented reality-based tool at baseline and week 8, with brief pulse assessments administered twice-weekly throughout the intervening period. Blood biomarkers will be collected via venipuncture at Quest Diagnostics (baseline and week 8). Physical activity and sleep data will be respectively monitored using Fitbit (all groups) and the Elemind headband (sleep and sleep + exercise groups), and light exposure will be tracked via the Lys device (sleep and sleep + exercise groups). Participants will also complete validated self-report surveys (e.g., PASE, CHAMPS–MET, PROMIS instruments) to capture psychosocial and behavioral variables at weeks 0 and 8. This multimodal approach will enable temporally-aligned, comprehensive data capture across digital and self-reported domains (see Table 3).

**Table 3 Tab3:** Timeline of questionnaires provided

Variable	Screening	Baseline	8-week
Basic Info Screening Form (eligibility criteria)	X		
Physical Activity Readiness Questionnaire (PAR-Q)	X		
Quick Mild Cognitive Impairment screen (QMCI), 6-item	X		
Demographic Questionnaire		X	
Chronic Health Questionnaire		X	X
PROMIS Self-reported Cognitive Functioning Behaviors Short Form		X	X
PROMIS Sleep Disturbance 4a		X	X
PROMIS Emotional Support 4a short form		X	X
PROMIS Depression 4a shot form		X	X
PROMIS Anxiety 4a short form		X	X
PROMIS Social Isolation 4a		X	X
General PROMIS Life Satisfaction 5a		X	
Cross Ethnic-Racial Identity Scale		X	
PASE Physical Activity Questionnaire (exercise and sleep + exercise interventions only)		X	X
CHAMPS-MET Physical Activity Questionnaire (exercise and sleep + exercise interventions only)		X	X

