### Measures and instruments

To capture a comprehensive and multidimensional view of participants’ cognitive, emotional, behavioral, and physiological profiles, the study will employ both survey-based instruments and digital device-based measures. Instruments will be categorized into predictor and outcome variables and will span psychosocial, cognitive, behavioral, and biological domains.

Self-report surveys will be administered at baseline (week 0) and at the 8-week follow-up by a trained research assistant or postdoctoral scholar via in-person visits or, if unable to come in person in the sleep-only group, by a secure video conference. These will include the PASE [22] and CHAMPS [23] questionnaires to assess physical activity and weekly caloric expenditure, respectively, for those in the exercise-only or sleep + exercise interventions. Additionally, each participant will complete all validated Patient-Reported Outcomes Measurement Information System (PROMIS) short-form questionnaires that measure sleep disturbance, self-reported cognitive functioning, emotional support, depression, anxiety, life satisfaction, and social isolation [21] at the baseline and post-intervention visits, except for the General PROMIS Life Satisfaction 5a questionnaire, which will be completed at the baseline visit only. Additional measures will include a Demographic Questionnaire, a Chronic Health Questionnaire, and the Cross Ethnic-Racial Identity Scale [44] to capture relevant sociodemographic and psychosocial predictors (see Table 3). Objective data will be collected via digital devices, including the Elemind Neuromodulation headband (sleep metrics), Fitbit Charge 5 (physical activity and heart rate), Lys sensor (light exposure), and the Digital Neuro-Signatures neuropsychological assessment (cognitive function). Blood-based biomarkers will be obtained through Quest Diagnostics to assess brain and cardiometabolic health for all participants at the baseline and post-intervention visits as well as AD-associated neuropathology for all participants at the baseline visit. The 6MWT will be used to assess changes in fitness and aerobic capacity. Together, these tools will enable high-resolution modeling of the relationships between behavior, biology, and cognitive health across all three study arms.

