#### Physical Activity Scale for the Elderly (PASE) questionnaire

The PASE Questionnaire will only be administered to participants assigned to interventions involving exercise. The PASE is a validated, self-report instrument that is widely used to assess physical activity. The PASE Questionnaire was originally designated for community-dwelling adults aged ≥ 65 years but has been subsequently validated in adults aged 45–64 years [45]; this questionnaire has demonstrated high test-retest reliability, with intraclass correlation coefficients (ICC) found to be *r* = 0.75 (95% CI = 0.69–0.80) over 3–7 weeks [22]. Short-interval reliability (10–14 days) has shown excellent reproducibility with ICCs, which range from 0.93–0.99 in prior work [46, 47]. Furthermore, construct validity is moderately supported: correlations with accelerometer-measured physical activity (steps, energy expenditure) range from *r* ≈ 0.30–0.61 [48]. While internal consistency varies across activity domains (α ≈ 0.69–0.99 [22, 46]), the total score remains robust for classifying overall activity levels in older populations. Given the robustness of the PASE questionnaire across older adult populations, similar reliability is expected in upper middle-aged adults (55–64 years).

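### The protocol gives two incompatible orders for randomisation and baseline assessment; on the order it works to, week-0 cognitive and PROMIS scores are taken after participants know their arm

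*Protocol article*

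**What the plan says.** The Randomization section of the protocol article sets a condition: "Participants will be eligible for randomization once all baseline questionnaires are completed".

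The Screening and consent section describes written consent at an in-person visit and continues: "Thereafter, prospective participants will be randomized into one of three arms and will receive intervention-specific, wearable devices". It then runs the 7-day screening week by assigned arm. It applies the eligibility results to people already allocated ("Prospective participants who are assigned to the sleep or sleep + exercise interventions and are determined to have good quality sleep after the onboarding period" are moved to exercise-only or excluded) and ends: "Subsequent to completing the onboarding screening period, eligible participants will be invited to complete an in-person baseline visit".

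The Baseline and follow-up visits section gives the same order: "After consent and randomization, participants will be onboarded in person to each intervention-specific device and observed for a 7-day period prior to the baseline visit".

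On timing of the measures, the Measures and instruments section says: "Self-report surveys will be administered at baseline (week 0) and at the 8-week follow-up by a trained research assistant or postdoctoral scholar". The arm sections place the full-length DNS assessment at week 0 and week 8. On which forms are given to whom, the PASE section says: "The PASE Questionnaire will only be administered to participants assigned to interventions involving exercise". The CHAMPS section and Table 3 say the same for CHAMPS.

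The Limitations section acknowledges that participants are not blinded. The Analysis plan makes the group × time interaction over baseline and week 8 the main test of efficacy.

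**The concern.** A site cannot require finished baseline questionnaires before randomising and also hold the baseline visit a week after randomising. This is not detail that a condensed article leaves to a fuller document; it is two statements that exclude each other.

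The order matters because the main test is a comparison of change. In a randomised comparison the baseline score is safe to use because it is fixed before the arm is known. If it is recorded afterwards, by someone who knows the arm, then disappointment, expectation or effort on a game-like test can move it, and the group × time term no longer starts from a baseline independent of allocation. In addition, anyone lost between allocation and the baseline visit is randomised but has no cognitive score at all.

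**Working it through.** The document gives no figure for this point, so the check is mainly of sequence.

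**1. Two orders.**

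| Step | Randomization section | Screening and consent; Baseline and follow-up visits |
|---|---|---|
| 1 | Consent | Consent |
| 2 | Baseline questionnaires | Randomisation and arm-specific devices |
| 3 | Randomisation | 7-day onboarding, with possible reassignment or exclusion |
| 4 | – | Baseline visit: DNS and questionnaires |

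**2. Can they be reconciled?** Only if the baseline questionnaires in the Randomization section meant the telephone forms. Table 3 rules this out: the Basic Info form, PAR-Q and QMCI are in its Screening column, and a different set is in its Baseline column. That set includes PASE and CHAMPS for the exercise-containing arms only, so which forms a person must complete depends on the arm. The condition cannot be carried out as written.

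**3. Which order is operative?** Allocation first. Device hand-out by arm, screening criteria by arm, reassignment of people already allocated, and arm-restricted PASE and CHAMPS all need it. The week-0 DNS and PROMIS scores then follow allocation by at least the 7 onboarding days.

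**4. What this does to the main contrast.** Suppose there is no true effect. Let knowledge of the arm create a between-arm difference b0 at week 0 and b8 at week 8, in SD of the score.

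- Bias in the change contrast = b8 − b0.
- Shift wholly transient (b8 = 0): bias = −b0.
- Half persists (b8 = b0/2): bias = −b0/2.
- Shift wholly persistent (b8 = b0): bias = 0.

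The fallback ANCOVA does not remove the problem. With equal variances and correlation ρ between the two times, its bias is b8 − ρ·b0. For b0 = b8 = 0.2 and ρ = 0.5 this is 0.2 − 0.1 = 0.1.

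**5. Illustration only.** For a pairwise comparison at 20 per arm, SE = √(2(1 − ρ)) × √(2/20), which is 0.316, 0.245 and 0.200 for ρ = 0.5, 0.7 and 0.8. The false-positive rate of a two-sided 5% test (normal approximation) under a net bias of size |b8 − b0| is:

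| Net bias (SD) | ρ = 0.5 | ρ = 0.7 | ρ = 0.8 |
|---|---|---|---|
| 0 | 5.0% | 5.0% | 5.0% |
| 0.1 | 6.2% | 6.9% | 7.9% |
| 0.2 | 9.7% | 12.9% | 17.0% |
| 0.3 | 15.8% | 23.2% | 32.3% |

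The documents give neither the net bias nor ρ; both are assumed. The table shows what would follow from a shift, not that one will occur.

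**6. Early leavers.** A mixed model fitted by maximum likelihood uses every observed score. A person with none at week 0 or week 8 contributes no row, so the intention-to-treat model omits that person despite randomisation.

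**The case against.** The strongest case against is that the consequence is easy to overstate. Most of that case stands. A reader might infer each of the following, and the documents do not support it:

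- **That a baseline shift passes one for one into the result.** This holds only if the shift has gone by week 8. Participants remain unblinded throughout, so some or all of it may persist and cancel. With a baseline taken before allocation, the persistent part would enter the contrast in full. It would then be part of the week-8 effect of open assignment, measured from a clean starting point, but the proposed order does not remove expectancy.
- **That staff bias the scores.** No section says whether staff at the baseline visit know the arm. It is likely, since they onboard people to arm-specific devices and give PASE and CHAMPS by arm, but it is an inference. The DNS is scored by algorithm and transmitted automatically, so the plausible route is the participant's own effort or expectation.
- **That all primary outcomes are affected.** NfL and the eight cardiometabolic markers are little open to effort or expectation, and the psychosocial PROMIS measures are tertiary. The DNS scores are the exposed primary outcomes.
- **That people re-screened for sleep-only are exposed for 14 days.** They spend the first week under a different assignment and know their final arm for about 7 days before baseline.
- **That voluntary losses before baseline differ by arm.** They may, but nothing in the document shows it.

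The Limitations section does plan a perceived-benefit covariate and expectancy sensitivity analyses. These are offered for the missing sham control and do not restore a pre-allocation baseline.

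None of this touches the contradiction itself.

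**Conclusion.** The contradiction is certain and rests on the text alone. The working order is allocation first, so the week-0 DNS and PROMIS scores are produced by participants who have known their arm for at least 7 days, and the baseline in the main test can depend on allocation.

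The size and direction of any resulting bias cannot be stated from the document; the rates above depend wholly on assumed values. That randomised people who leave before the baseline visit are absent from the cognitive mixed model follows directly from the sequence. The point should be corrected before enrolment, because a baseline cannot be collected again once the arm is known.

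**What to change.** State one order in all three sections: consent; full-length DNS, PROMIS and the other arm-independent baseline questionnaires at the existing in-person consent visit; REDCap allocation opened; devices handed out; onboarding week. Define the scores from the consent visit as the week-0 values for the mixed model.

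PASE and CHAMPS can stay at the end of the onboarding week. PASE asks about the previous 7 days and is meant to be compared with Fitbit, so at the consent visit its recall window would fall before Fitbit wear starts. Reword the Randomization section to exempt these two forms and identify their baselines as post-allocation.

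**Costs.** The consent visit grows by about 20 minutes for the DNS plus the questionnaires. Some people later found ineligible will have been tested. The cognitive baseline falls a week or more earlier relative to the blood draw and the start of intervention, and longer still for those re-screened into sleep-only, so the interval would differ somewhat by arm.

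**What this leaves open.** It does not resolve the separate problem that exclusion and reassignment by arm happen after allocation. Running the onboarding week and the baseline visit for everyone before randomising would address both, but would need a headband for every prospective participant.

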#### Baseline and follow-up visits

Data will be collected at baseline, biweekly, and at the 8-week follow-up to assess changes in sleep, exercise, biomarkers, and cognition. After consent and randomization, participants will be onboarded in person to each intervention-specific device and observed for a 7-day period prior to the baseline visit to establish baseline sleep patterns and/or physical activity levels relevant for each assigned intervention and to ensure all eligibility criteria are satisfied. Cognitive function will be measured using an augmented reality-based tool at baseline and week 8, with brief pulse assessments administered twice-weekly throughout the intervening period. Blood biomarkers will be collected via venipuncture at Quest Diagnostics (baseline and week 8). Physical activity and sleep data will be respectively monitored using Fitbit (all groups) and the Elemind headband (sleep and sleep + exercise groups), and light exposure will be tracked via the Lys device (sleep and sleep + exercise groups). Participants will also complete validated self-report surveys (e.g., PASE, CHAMPS–MET, PROMIS instruments) to capture psychosocial and behavioral variables at weeks 0 and 8. This multimodal approach will enable temporally-aligned, comprehensive data capture across digital and self-reported domains (see Table 3).

**Table 3 Tab3:** Timeline of questionnaires provided

Variable	Screening	Baseline	8-week
Basic Info Screening Form (eligibility criteria)	X		
Physical Activity Readiness Questionnaire (PAR-Q)	X		
Quick Mild Cognitive Impairment screen (QMCI), 6-item	X		
Demographic Questionnaire		X	
Chronic Health Questionnaire		X	X
PROMIS Self-reported Cognitive Functioning Behaviors Short Form		X	X
PROMIS Sleep Disturbance 4a		X	X
PROMIS Emotional Support 4a short form		X	X
PROMIS Depression 4a shot form		X	X
PROMIS Anxiety 4a short form		X	X
PROMIS Social Isolation 4a		X	X
General PROMIS Life Satisfaction 5a		X	
Cross Ethnic-Racial Identity Scale		X	
PASE Physical Activity Questionnaire (exercise and sleep + exercise interventions only)		X	X
CHAMPS-MET Physical Activity Questionnaire (exercise and sleep + exercise interventions only)		X	X
**Biomarker data**			
Total cholesterol		X	X
High density lipoproteins		X	X
Low density lipoproteins		X	X
Triglycerides		X	X
High-sensitivity C-reactive protein		X	X
Glycated hemoglobin		X	X
C-peptide		X	X
Insulin		X	X
Neurofilament light chain		X	X
Amyloid beta peptide 1–42		X	
Amyloid beta peptide 1–40		X	
Amyloid beta peptide 1–42/amyloid beta peptide 1–40 ratio		X	
Phosphorylated tau at threonine 217		X	

Table outlines the timeline for the collection of information from questionnaires and blood panels. *PROMIS*, Patient-Reported Outcomes Measurement Information System.

Participants who provided written consent and are found to be eligible for participation at the conclusion of the 7-day onboarding screening period will undergo the following procedures in accordance with the intervention to which each subject was assigned:

### Interventional group 1 (exercise only)

Participants randomized to the exercise-only group will engage in an 8-week, home- and site-based exercise intervention designed for older adults across a range of cognitive and physical function levels. All site-based sessions will occur in-person at the study facility under supervision of trained staff. Each week, participants will attend two 60-minute structured exercise sessions, consisting of aerobic training and resistance training. On the remaining five days when subjects will not engage in structured exercise, subjects will be asked to engage in 30 minutes of moderate-intensity walking activities. In-lab exercise protocols will be fully standardized to ensure consistency of exercise dosage and fidelity across participants. The target exercise load will be 270 minutes of moderate-intensity exercise weekly for 8 weeks. Although considered short-term exercise, this exercise dosage has been shown to improve cerebral blood flow, regional brain volume, and brain-protective trophic factors [32].

Participants will begin with a 7-day onboarding period, during which participants will wear the Fitbit continuously to establish baseline physical activity levels and to ensure initial eligibility criteria are satisfied. Subsequent to this initial observation and screening phase, subjects will participate in biweekly, in-person exercise sessions, which will be comprised of 60 minutes of stretching, aerobic, and resistance training exercises. Specifically, exercise sessions will consist of a 10-minute warm-up, followed by 20 minutes of moderate-intensity aerobic exercise at 60–75% of estimated maximum heart rate (MHR). MHR will be estimated using Tanaka’s formula (maxHR = 208-(0.7*age)) [33], and the target heart rate (THR) will be calculated using Karvonen’s formula to account for resting heart rate (RHR), where THR = ((MHR-RHR)*% intensity) + RHR [34]. Moderate-intensity aerobic training will be followed by 20 minutes of resistance training of major muscle groups with an emphasis on lower extremity resistance training one day each week and upper extremity resistance training at the second in-person session weekly. Exercise load will be at 60–80% of an estimated one repetition max using American College of Sports Medicine Guidelines [35]. Muscle groups that will be trained include biceps, triceps, deltoid, and latissimus dorsi for the upper extremity, and quadriceps, hamstrings, and gastrocnemius/soleus for the lower extremity. Resistance training exercises targeting the trunk will also be incorporated. Each exercise session will then conclude with 10 minutes of post-exercise stretching.

